## Oversight and monitoring

### Composition of the coordinating center and trial steering committee {5d}

The steering committee, made up of eight academic investigators, developed the study protocol, will have full access to the interim data, is responsible for the decision to stop the trial, will publish the results, and wrote the manuscript. The committee members will vouch for the accuracy and completeness of the data reported. Endpoint adjudication will be performed by the investigators at the participating centers. The DMC may be asked to evaluate equivocal cases where the assignation of an outcome requires the judgment of an oncologist. Data management will be carried out by the CRO.

Steering Committee: [name], [name], [name], [name], [name], [name], [name] and [name].

### Composition of the data monitoring committee, its role and reporting structure {21a}

The DMC is composed of 3 members: an HIV specialist, a statistician, and an oncologist. The DMC will perform the interim analyses for futility, safety, and efficacy.

### Adverse event reporting and harms {22}

Possible adverse events and other unintended effects of the trial interventions will be reported by the investigators using the electronic database notebook of the study. In addition to unnecessary interventions, expected harms of the study include the potential complications associated with the invasive interventions derived from the abnormal findings observed in the diagnostic tests. Among the most frequent, pneumothorax or bleeding occurring after biopsy of a suspected malignant lung nodule found in the CT scan; bleeding after biopsy of a lesion found during anoscopy or colonoscopy (the latter, if indicated if positive fecal occult blood test), bacteremia/sepsis after prostate biopsy performed because of abnormal PSA values, etc. All harms occurring during the study will be reported, regardless of whether they were expected or not. Severe adverse events (SAE) need to be reported to the monitor of the study in a maximum of 24 h. The monitor will notify the SAEs to the coordinators of the study. The medical monitor will also be responsible to review the reported safety data, to obtain all the useful safety information not reported by the investigators and to advice the coordinators about violations of the protocol by any center and to document it. Harms will be reported in trial publications in the “Results” section of the manuscript

### Frequency and plans for auditing trial conduct {23}

Biannual reviews will be carried out by the CRO on all the data recorded by the researchers in the electronic database notebook.

### Plans for communicating important protocol amendments to relevant parties (e.g., trial participants, ethical committees) {25}

Important protocol amendments will be communicated to relevant parties: investigators, ethical committees, trial participants, and trial registries.

### Dissemination plans {31a}

Trial results will be communicated to healthcare professionals, participants, the public, and other relevant groups, via publication or other data sharing arrangements.

## Discussion

Related to general population, PLWH are at higher mortality risk due to screenable cancer [30]. Increased mortality can result from higher incidence or late diagnosis, the latter amenable to improved screening. However, the benefits and harms associated with cancer screening in PLWH are unclear and may differ compared with uninfected persons. This trial will help to determine whether the benefits of the enhanced screening outweigh the harms and if it is cost-effective for the Public Health Services.

Although the ideal outcome measure would be mortality due to cancer, with our sample size, we will not reach the number of patients needed to detect differences in mortality between both groups. Hence, we established as a main outcome measure the detection of a greater number of cancers in early stages. It is unlikely that a randomized controlled trial of screening will be conducted with enough power to determine the cancer mortality reduction among the HIV-infected population. This trial has other limitations. There could be differences in baseline NADCs screening in different centers. Attempts will be made to correct these differences by redefining the protocol of the control group using the baseline screening data of the baseline survey trying to unify the screening in that group. Additionally, as it is a controlled study with a parallel group, there may be a risk of benefit from the control group due to imitation of the intervention group. After the first interim data analysis and if strictly necessary, a historical control group can be included prior to the start of the intervention group.

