### Trial design {8}

This protocol has been designed as a multicenter, randomized, parallel-group, and superiority trial.

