## Statistical methods

### Statistical methods for primary and secondary outcomes {20a}

The primary efficacy analysis will be the comparison of the proportion of cancers diagnosed at an early stage (1 and 2) in each group following the principle of intent to screen, defined as patients who accept to participate in the study and sign the informed consent, regardless of whether they are subsequently excluded due to loss of follow-up, non-adherence to study procedures, unwillingness to remain in the study, death, etc. A per protocol analysis including patients who complete the study will also be performed. A sample size of 2319 patients in each group has been calculated (expected incidence of early cancer 2% and 1% in enhanced and conventional groups, respectively; statistic power 80%; losses to follow-up 20%). Missing observations in the variables will be ignored in the analysis.

The secondary efficacy analysis will include the comparison of the incidence of cancer at any stage or unknown stage and the incidence of new cases of cancer diagnosed at stage 1 and 2 related to all new cases of cancer diagnosed.

The secondary safety analysis will compare the number of unnecessary invasive procedures, the rate of adverse events and severe adverse events, and overall mortality and mortality from cancer in both groups.

The secondary cost-utility analysis will be carried out following the recommendations of the guide for the economic evaluation of health technologies in Spain from the perspective of Spanish National Health System. The incremental cost-effectiveness ratio will be calculated, which is a measure of contrast between the increase in costs and the increase in effectiveness between the different screening alternatives compared. Statistical uncertainty will be expressed as the 95% confidence interval. Random samples of 100 patients from each group replaced 10,000 times will be projected on a graph to generate the increase in QALYs (quality-adjusted life year), the increase in costs, and the cost-effectiveness curve.

The analyses will be performed by a statistician blinded to patients’ allocation using the statistical packages SPSS® v.17 or higher, and R® 3.3 or higher. The statistical significance is set at *p* < 0.05.

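### A historical control group may be added after the first interim analysis, with no objective trigger and no stated role in the analysis

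*Protocol article*

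**What the plan says.** Trial design {8} declares a "multicenter, randomized, parallel-group, and superiority trial". Statistical methods {20a} defines the primary efficacy analysis as the "comparison of the proportion of cancers diagnosed at an early stage (1 and 2) in each group following the principle of intent to screen" and mentions no historical patients.

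The limitations paragraph of the Discussion makes two further provisions:

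- **Contamination.** It warns that "there may be a risk of benefit from the control group due to imitation of the intervention group" and continues: "After the first interim data analysis and if strictly necessary, a historical control group can be included", drawn from the time before the intervention began.
- **Differences between centres.** It proposes to correct these by "redefining the protocol of the control group using the baseline screening data of the baseline survey trying to unify the screening in that group".

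Three other statements bear on the first provision. The section on blinding {17a} says that the trial is open label. Interim analyses {21b} plans looks for futility, safety and efficacy every 12 months and has no prespecified stopping rules. The section on the steering committee {5d} says that this committee "will have full access to the interim data, is responsible for the decision to stop the trial".

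**The concern.** The contamination remedy is an option to bring in a non-randomised comparator, and its timing is tied to an interim analysis that includes efficacy. The article does not say what would make the step necessary, who would decide, which patients would be used beyond their preceding the intervention, or what the group would do in the analysis.

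A small interim difference between arms can mean that controls are being screened like the enhanced arm, or that the enhanced programme adds little. Nothing in the article separates the two. People who have seen the interim results could therefore choose a further comparator because the randomised one looks unfavourable.

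Historical patients are not protected by randomisation. They would come from before recruitment began in June 2019, and so from before the pandemic disruption described under Trial status. The primary outcome is detection of cancer at stage 1 or 2, which depends on how intensively people are examined. A group observed under other practice could differ on it for reasons unrelated to the intervention. At stake are the type I error rate and the randomised basis of any superiority claim.

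**Working it through.** **1. The plan's own figure.** This point has no stated number of its own, but the planned size per arm is an input. Sample size {14} gives 2% versus 1%, 80% power, a one-sided test, 20% loss and 2,319 per arm. The usual formula is

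n = [z_α √(2p̄(1−p̄)) + z_β √(p₁(1−p₁) + p₂(1−p₂))]² / (p₁−p₂)²

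With p̄ = 0.015, z_α = 1.645 and z_β = 0.842, n = (0.2828 + 0.1446)² / 0.0001 ≈ 1,826. Dividing by 0.8 gives 2,283, which is 1.6% below 2,319. The two-sided 0.05 version without inflation for loss gives exactly 2,319. The sidedness is therefore uncertain, and both versions are shown below.

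**2. Inputs to the illustration.**

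- True early-stage rate of 1.0% in both randomised arms, i.e. no effect. This is the control rate in Sample size {14}.
- 2,319 per randomised arm, without attrition.
- Historical rate of 0.65% (assumed). CoRIS gives 0.43 per 100 person-years at any stage; 3 × 0.43% ≈ 1.3%, and half of that is 0.65%. The half has no source in the document. A milder 0.8% is also shown.
- Historical group of 2,319 (assumed equal to one arm) or about 10,409 (31,228 person-years / 3).

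**3. Formula.** With D = p_E − p_C, the probability of declaring the enhanced arm superior is Φ[(D − z·SE₀)/SE₁]. SE₀ uses the pooled rate and SE₁ the separate rates.

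*Historical patients replace the controls, rate 0.65%, two-sided 0.05 (z = 1.96):*

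- Historical n = 2,319: SE₀ = SE₁ = 0.002656; (0.0035 − 0.005206)/0.002656 = −0.64; Φ = 0.26.
- Historical n = 10,409: SE₀ = 0.001933, SE₁ = 0.002211; (0.0035 − 0.003789)/0.002211 = −0.13; Φ = 0.45.

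*Historical patients pooled with the randomised controls, rate 0.65%:*

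- Historical n = 2,319: combined control rate 0.825% on 4,638; D = 0.00175; Φ = 0.12.
- Historical n = 10,409: combined rate 0.714% on 12,728; D = 0.00286; Φ = 0.33. Simulation gives 0.32.

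**4. Results** (probability of false superiority, from the formula and simulation):

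| Historical rate | Historical n | Replace, two-sided 0.05 | Pool, two-sided 0.05 | Replace, one-sided 0.05 |
|---|---|---|---|---|
| 1.0% (no drift) | 2,319 / 10,409 | about 2.5–3% | about 2.5–3% | about 5% |
| 0.8% | 2,319 | 10–11% | 6.5% | 18% |
| 0.8% | 10,409 | 17–18% | 13.5% | 26% |
| 0.65% | 2,319 | 26% | 12% | 37% |
| 0.65% | 10,409 | 44–45% | 32% | 55–56% |

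The nominal rate in favour of the enhanced arm is 2.5% for the two-sided test and 5% for the one-sided test.

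**5. Effect of the option alone.** This second simulation has no effect, 1,855 evaluable per arm (2,319 × 0.8), an equal historical group and a one-sided 0.05 test. The randomised comparison alone gives 5.0%. Suppose success is claimed when either the randomised comparison or a second comparison is significant. With no drift at all, the rate is 7.4% if the second comparison pools the historical patients and 8.8% if it uses them alone. At a historical rate of 0.8% these become 11.5% and 18.2%. Having a choice of comparator inflates the error even when the historical group is perfectly comparable.

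**The case against.** Several counter-arguments have force.

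- **The text says that a historical group can be included.** A reader might infer that it would replace the randomised control arm. The document does not say so, and both the design statement and the primary analysis remain randomised and parallel-group. This stands. The replacement figures are the upper case and the pooled figures are nearer to the wording. It does not remove the problem, because an undefined role permits either use.
- **Redefining the control group's screening is a separate matter.** A reader might infer that it, too, follows the interim look. The Discussion ties it to the baseline survey of screening practice, with no reference to outcomes and no timing. Allocation is 1:1 in blocks of twenty, with balance by sex and centre, so any change over time would meet concurrent enhanced patients. It would alter the contrast being estimated but is not shown to bias it. This stands.
- **The trigger could be benign.** Imitation might be judged from the screening tests that controls received and not from outcomes. That is possible, but the article does not say so.
- **The direction of bias is not documented.** Historical screening is not described. If the pandemic reduced detection during the trial, earlier patients could show more early cancers; at a historical rate of 1.2%, full replacement would favour the enhanced arm in under 0.5% of trials (two-sided 0.05). This stands. Bias towards superiority is plausible but not established.
- **The illustration sets a planning rate against a halved cohort rate.** The gap of 0.35 percentage points is assumed. This stands, and the figures are labelled accordingly.
- **A fuller protocol or SAP may settle the role.** If so, the article needs only to be brought into line. The objection here is to an option that the article expressly grants.

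**Conclusion.** The point holds for the historical control group. The article permits a non-randomised comparator to enter after an interim analysis that includes efficacy, with no objective trigger and no analysis role, in an open-label trial whose steering committee sees interim data in full. Used as written, the option could supplement or displace the randomised comparison and raise the false-positive rate.

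The size depends on quantities that the documents do not give. Under the assumed 0.65%, false superiority is about 26–45% with full replacement and about 12–32% with pooling, against 2.5% nominal (two-sided 0.05). At 0.8% it is about 10–18% and 6.5–13.5%. With no drift, free choice between analyses alone moves a one-sided 5% test to about 7–9%.

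The documents do not support the stronger readings that the randomised comparison will be replaced, that the control arm will be redefined in the light of outcomes, or that the bias must favour the enhanced arm. The redefinition is a lesser, separate matter: its basis is acceptable, but its timing is left open although recruitment has been running since June 2019.

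**What to change.** Choose one of two wordings for the historical group:

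1. Delete it from the efficacy analysis.
2. State that the primary and all confirmatory efficacy conclusions use concurrently randomised controls only. Any comparison with historical CoRIS patients is then descriptive or supportive, with its trigger, source population, period and method fixed before anyone involved in the decision sees interim data.

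If the first interim analysis has already taken place, option 1 is the cleaner choice, because a trigger written now can no longer be shown to be independent of the results.

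Separately, state that any redefinition of control-arm screening from the baseline survey is completed and dated without reference to outcome data.

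The cost is a short protocol amendment, with no new data collection and no change to the sample size calculation. The downside is that contamination stays in the primary result and dilutes the estimated difference. That is what an intent-to-screen comparison is meant to show, but it can cost power if imitation is widespread.

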## Trial status

The current protocol is the 1.1 version. The recruitment began on 25 June 2019, but unfortunately, it was disrupted by the COVID-19 pandemic state. Recruitment has been restarted in the different centers according to the COVID-19 pandemic situation on each area. Because of the overall delay in the recruitment, the duration of the study has been extended. The approximate date when the recruitment will be completed is by the end of December 2022.

[figure not shown]

## Abbreviations

ART: Antiretroviral therapy
CoRIS: Cohort of the National AIDS Research Network
CRO: Clinical Research Organization
EACS: European AIDS Clinical Society
GP: General population
HBV: Hepatitis B virus
HCC: Hepatocellular carcinoma
HCV: Hepatitis C virus
HPV: Human papillomavirus
LDCT: Low-dose computed tomography
MSM: Men who have sex with men
NADCs: Non-AIDS-defining cancers
NHS: National Health Service
QALY: Quality-adjusted life year
PSA: Prostate-specific antigen
PLHIV: Population living with the human immunodeficiency virus
RIS: Spanish AIDS Research Network
